### Study objective

#### Primary and secondary outcomes

The primary outcome of this study is the changes in rSO_2_ within 24 h postoperatively. See Table 2.

The secondary outcomes are as follows (the corresponding parameters are listed in Tables 2 and 3):
Changes between preoperative and postoperative LUSs in patients. LUSs will be used to evaluate postoperative atelectasis. The patient’s chest is divided into 12 quadrants. Each of the 12 quadrants is assigned a score of 0 to 3 according to a modified grading system (Table 4). The LUS score (0–36) is then calculated by adding up the 12 individual quadrant scores, with higher scores indicating more severe atelectasis [21].The mean arterial pressure changes during intraoperative pulmonary protective ventilation.The partial pressures of oxygen (PaO_2_) and carbon dioxide (PaCO_2_), oxygenation index (OI), and lactic acid level (Lac) in arterial blood changes during intraoperative pulmonary protective ventilation.The amount of vasoactive drugs and blood loss will be compared in the two groups during surgery.Intraoperative brain relaxation, which will be scored by the neurosurgeons after opening the cranium and before opening the dura. They will use a 4-point scale [22]: 1, completely relaxed; 2, satisfactorily relaxed; 3, firm brain; 4, bulging brain.The secondary operation rate in 1 week after surgery (reoperation rate).

**Table 2 Tab2:** Comparison of rSO_2_, PaO_2_, PaCO_2_, OI, Lac, and MAP

		T0	T1	T2	T3
rSO_2_	C group				
	P group				
PaO_2_	C group				
	P group				
PaCO_2_	C group				
	P group				
OI	C group				
	P group				
Lac	C group				
	P group				
MAP	C group				
	P group				

*T0* before anesthesia, *T1* before dura opening, *T2* after dura closing, *T3* 24 h after surgery, *rSO*_*2*_ regional cerebral oxygen saturation, *PaO*_*2*_ partial pressure of oxygen, *PaCO*_*2*_ partial pressure of carbon dioxide, *OI* oxygenation index, *Lac* lactic acid level, *MAP* mean arterial pressure

**Table 3 Tab3:** Perioperative parameters

	C group	P group
Tidal volume, ml		
Individual PEEP, cmH_2_O		
Duration of anesthesia, min		
Duration of operation, min		
Duration of dura opening, min		
Tumor size (maximum diameter)		
Brain relaxation scale (T1)		
Brain relaxation scale (T2)		
Lung ultrasound score (T0)		
Lung ultrasound score (T3)		
Volume of total fluid, ml		
Amount of bleeding, ml		
Volume of urine, ml		
Dosage of vasoactive agent, mg		
Reoperation rates

**Table 4 Tab4:** Modified lung ultrasound scores

Quotation	Normal aeration	Small loss of aeration	Moderate loss of aeration	Severe loss of aeration
	0	1	2	3
Modified lung ultrasound score	0–2 B lines	≥ 3 B lines OR 1 or multiple small subpleural consolidations separated by a normal pleural line	Multiple coalescent B lines OR multiple small subpleural consolidations separated by a thickened or irregular pleural line	Consolidation OR small subpleural consolidation of > 1 × 2 cm in diameter

Lung ultrasound scores can be calculated by adding up the 12 individual pulmonary quadrant scores yielding a score between 0 (no aeration loss) and 36 (complete aeration loss)

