## Abstract

**Objective:**

The objective of this trial is to investigate the effects of protective lung ventilation on regional cerebral oxygen saturation (rSO_2_) during dura opening, that is from Ta (after dura opening) to Tb (before dura closing), in patients undergoing intracranial tumor surgery.

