### Study intervention

#### Related parameter setting during operation

All patients will be randomly allocated to the C group or the P group according to the computer-generated random number table. In the C group, tidal volume (VT) will be set at 8 ml/kg of predicted body weight, with PEEP = 0, and recruitment maneuvers will not be used. The predicted body weight is calculated as follows: for men, 50 + 0.91 (height in centimeters – 152.4); and for women, 45.5 + 0.91 (height in centimeters – 152.4) [18]. In the P group, VT will be set at 6 ml/kg of predicted body weight combined with individualized PEEP during intraoperative dura mater opening [6, 7], but in other periods of general anesthesia, VT will be set at 8 ml/kg of predicted body weight. For the titration method of individualized PEEP [19], VT and respiratory rate will be fixed at 6 ml/kg and 15 beats per minute during PEEP trial. Titration can only begin once the dura is opened. The titration for the individual PEEP can then be initiated by increasing PEEP from 0 to 10 cm H_2_O incrementally. Each PEEP level (0, 1, 2, 3, 4, 5, 6, 7, 8, 9, 10 cmH_2_O) will be maintained for 1 min, and the pulmonary compliance of the last cycle will be recorded at each PEEP level. The PEEP value at the highest compliance will then be selected as the individual PEEP of the patient.

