Peripheral venous access will be established after the patient enters the operating room. If necessary, central venous access will be established. Noninvasive blood pressure (NBP), electrocardiogram (ECG), heart rate (HR), oxygen saturation (SpO_2_), and bispectral index (BIS) will be routinely monitored. Radial artery catheterization under local anesthesia will be used to monitor invasive arterial pressure and collect blood samples. All of the above data will be collected completely. Fentanyl 5 μg/kg, etomidate 0.3 mg/kg, rocuronium 0.6 mg/kg will be used for induction and will be started after oxygen flow of 0.1 L/kg/min has been given by mask for 2 min. Volume-controlled mechanical ventilation will be conducted with a Primus anesthesia machine (Dräger, Lübeck, Germany) after the endotracheal catheter is inserted to a correct position. The VT will be set at 8 ml/kg of predicted body weight, the inhalation oxygen fraction (FiO_2_) will be set at 0.5, the inhalation-expiration ratio (I:E) = 1:2, and the fresh gas flow will be set at 1 L/min. The respiration rate will be adjusted according to the result of end-expiratory carbon dioxide (ETCO_2_), and the end-tidal CO_2_ pressure (PetCO_2_) will be maintained between 30 and 35 mmHg. There will be 1% sevoflurane combined with propofol and remifentanil to maintain anesthesia, and the BIS value will be maintained at 45–55. During the operation, intermittent injection of fentanyl and rocuronium will be used to deepen the anesthesia. Extubation indications are that patients are awake and cooperating and muscle relaxation monitoring train-of-four (TOF) stimulation > 90% [20]. Intraoperative fluid intake and urine volume will be monitored closely. The level of rSO_2_ will be recorded in the tumor surgery area of the patients before anesthesia (T0), before dura opening (T1), after dura closing (T2), and 24 h after surgery (T3). Arterial blood of the patients will be collected for blood gas analysis. Lung ultrasound scores (LUSs) will be performed at T0 and T3. The degree of brain relaxation at T1 and T2 will be evaluated by the surgeon using the brain relaxation scale. The amounts of vasoactive drugs used and blood loss will be recorded during surgery. The duration of operation and reoperation rate will be recorded.

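### The stated objective is rSO2 while the dura is open, but the primary outcome is an unspecified change within 24 h after surgery, and the text and Table 2 list no rSO2 reading in the open-dura window

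*Protocol article*

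**What the plan says.** - **Objective (Abstract).** The trial is to study rSO2 "during dura opening, that is from Ta (after dura opening) to Tb (before dura closing), in patients undergoing intracranial tumor surgery". The labels Ta and Tb are not used again in the article's text or tables.
- **Primary outcome (Abstract, Methods; Primary and secondary outcomes).** "The primary outcome of this study is the changes in rSO_2_ within 24 h postoperatively", with a pointer to Table 2.
- **Measurement times (Related parameter setting during operation; Table 2).** rSO2 is recorded "before anesthesia (T0), before dura opening (T1), after dura closing (T2), and 24 h after surgery (T3". Table 2 has the same four columns for rSO2, PaO2, PaCO2, oxygenation index, lactate and MAP.
- **Intervention (Related parameter setting during operation).** In the P group, "VT will be set at 6 ml/kg of predicted body weight combined with individualized PEEP during intraoperative dura mater opening". PEEP titration starts only after the dura has been opened, and tidal volume is 8 ml/kg, as in the C group, at other times under anesthesia.
- **Secondary outcomes.** One is the "mean arterial pressure changes during intraoperative pulmonary protective" ventilation; the blood-gas outcomes are worded the same way.
- **Sample size and justification.** The planning value is 3.6 ± 4.1, described as a difference in brain oxygen saturation before and after surgery. It leads to 44 patients.

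**The concern.** The objective and the primary outcome describe different quantities. One is cerebral oxygenation while the two ventilation strategies are running; the other is a change on an unstated scale over the day after surgery. A trial that follows the outcomes section and Table 2 to the letter would finish without an rSO2 value from the period named in its objective.

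Two things are at stake. First, interpretation: a null result at T2 or T3 would not exclude an effect while the dura was open. Second, choice: with no baseline, time point or summary fixed, the primary comparison could be selected after the data are seen. The Statistics section does not settle this, since it provides ANOVA with post hoc comparisons across time points and names none as primary.

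The blood-gas secondary outcomes share the first problem. They are worded as changes during protective ventilation, yet no sample is listed during it.

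**Working it through.** **1. Place each listed reading against the intervention window.**

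| Reading | Relation to the open-dura window |
|---|---|
| T0, before anesthesia | before |
| T1, before the dura is opened | before; titration has not begun |
| Ta to Tb (Abstract objective only) | inside; no reading listed in the text or Table 2 |
| T2, once the dura is closed | after; P-group tidal volume is 8 ml/kg again |
| T3, the day after surgery | after |

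None of the four listed readings lies inside the window.

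**2. Count the contrasts that could be primary.** Two possible baselines (T0, T1) times two later readings (T2, T3) gives 2 × 2 = 4. Read literally, only T3 is clearly postoperative, which still leaves two baselines. If all four were tested at 5% and the best one reported, the family-wise error could be at most 4 × 0.05 = 20%. That is an upper bound; correlation between the contrasts makes the true figure lower.

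**3. Reproduce the plan's own sample size.** Inputs from Sample size and justification: difference 3.6, SD 4.1, α = 0.05, power 0.80. Two-sided testing is assumed, because sidedness is not stated.

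- Standardized difference: d = 3.6 / 4.1 = 0.878.
- Normal approximation: n per arm = 2(1.960 + 0.842)² / 0.878² = 20.4, so 21 per arm and 42 in total.
- Two-sample t-test (noncentral t): 21.37, so 22 per arm and **44 in total**, as stated.
- Power at 22 per arm: noncentrality 0.878 × √(22/2) = 2.91 on 42 degrees of freedom, power **0.812**.

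The 44 is therefore what a two-arm t-test gives when 3.6 is the between-arm difference and 4.1 the SD. The plan attaches those values to a before/after-surgery difference. It offers no effect or SD for a Ta-to-Tb change, a Tb value or an in-window mean.

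**4. Illustration only.** Suppose, contrary to the plan's description, that 3.6 were the in-window effect, that SD stayed at 4.1, and that a later reading kept only a fraction f of it. Power at 22 per arm would be:

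| f | 1.00 | 0.75 | 0.50 | 0.25 |
|---|---|---|---|---|
| Power | 0.81 | 0.57 | 0.30 | 0.11 |

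The documents give no value for f, so this table shows sensitivity to an assumption and is not an estimate.

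**The case against.** **The broader aim.** The last paragraphs of the Background, the Abstract's Discussion and the opening of the Discussion attach the open-dura period to the ventilation, not to the rSO2 reading. On that reading the question is whether open-dura ventilation alters rSO2 at all. T1 and T2 bracket the window, so a randomized T1-to-T2 comparison would be informative about any effect that outlasts closure. The Background also says alveolar collapse can persist for days, which gives later readings a rationale. This stands. A reader might infer that the trial cannot answer its question at all; the documents do not support that. But the T1-to-T2 contrast is not named as primary, and the Abstract's objective does fix the reading inside the window.

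**Fading of the effect.** A reader might also infer that any effect is mostly gone by T2 or T3 and that power therefore drops to 30% or 11%. Nothing in the article says how fast an rSO2 effect fades, how long after closure T2 is read, or when PEEP stops in the P group. The planning value is itself described as before versus after surgery, so discounting it as an in-window effect runs against its own label.

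**Fig. 1.** The schedule figure is not shown and might list Ta and Tb. This limits the claim to the text and Table 2. The primary outcome would still differ from the objective.

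**MAP.** Arterial pressure is monitored invasively and the text says the monitoring data will be collected completely, so in-window MAP probably exists, although Table 2 tabulates only T0 to T3. The criticism of the secondary outcomes holds for the blood gases.

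**The sample-size wording.** It reports a planning value, not an endpoint definition, and could fit a T0-to-T3 change. That is fair; it shows that the intended contrast has to be guessed.

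**Conclusion.** The point holds as an inconsistency between objective and primary outcome, with the primary contrast left open. On the text and Table 2, none of four listed rSO2 readings falls between Ta and Tb, at least four contrasts could be called primary, and the blood-gas outcomes said to be measured during protective ventilation have no listed sample there. The sample size is arithmetically sound (44 patients, about 81% power) for the difference it describes, but it is not justified for the Abstract's objective.

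The conclusion rests on Fig. 1 not adding in-window readings. It does not rest on any claim that the effect fades or that power is lost; those would need a retained fraction that the documents do not give. It matters enough to settle before the data are analyzed, because the primary endpoint determines what either a positive or a null result means.

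**What to change.** **Preferred.** Record rSO2, MAP and a blood gas at Ta and Tb. Make one endpoint primary: the between-arm difference in rSO2 at Tb, or in mean rSO2 over Ta to Tb, adjusted for T1. Make T2 and T3 secondary.

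**Alternative, if in-window values cannot be obtained.** Reword the Abstract's objective to match one named contrast, such as the between-arm difference in change from T1 to T2, and reword the blood-gas secondary outcomes to match the times sampled.

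**In either case:**
- Use one definition in the Abstract (Objective and Methods), the measurement schedule, the outcomes section, Table 2, the sample-size section and the registry entry.
- Justify 3.6 and 4.1 again for the chosen endpoint and recompute the sample size if they change.
- State how patients already recruited without Ta and Tb readings enter the primary analysis.

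**Cost.** A protocol and registry amendment during recruitment, extra sampling points, and possibly missing in-window data for early patients. The measurement burden is small: the Discussion describes NIRS as continuous and noninvasive, and an arterial catheter is already planned. Whether more patients are needed cannot be said until an effect and SD are given for the new endpoint.

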Up to the present, in consideration of the risks associated with PEEP and recruitment maneuvers, there are no correlative randomized controlled trials to explore the efficacy and safety of intraoperative pulmonary protective ventilation strategies in patients undergoing craniotomy. However, due to the disappearance of ICP after the dura opening during craniotomy, an individualized protective pulmonary ventilation strategy may avoid adverse effects on cerebral perfusion. The purpose of this study is to evaluate the effects of PLV strategies with individualized PEEP during dura opening on rSO_2_ in patients undergoing intracranial tumor surgery. Other outcomes include intraoperative brain relaxation, lung ultrasound scores 24 h after surgery, the reoperation rate within 1 week after operation, the amount of blood loss, and dosage of vasoactive drugs during surgery.

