### Sample size and justification

We calculated the sample size through the website http://www.sample-size.net/sample-size-proportions/.

The difference in brain oxygen saturation before and after surgery was 3.6 ± 4.1, α = 0.05, β = 0.2 [7]. Based on this, it can be calculated that the sample size required for our study is 44 cases. Considering a 20% shedding rate, a total of 53 participants (44 + 44*20%) need to be recruited. Due to the 1:1 distribution ratio, a total of 54 cases will be recruited.

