### Statistics

The SPSS 19.0 software package for Windows (SPSS, Inc., Chicago, IL, USA) will be used for all statistical analyses. The quantitative variables will be expressed as mean ± standard deviation (SD) or median (interquartile range [IQR]) and analyzed by using the analysis of variance (ANOVA) or Mann-Whitney *U* test. Multiple comparisons among continuous variables at different time points will be performed using the Student-Newman-Keuls method for post hoc test. The incidence of reoperation rate will be expressed as the number of patients (percentage) and be analyzed by using the chi-square (χ^2^) test. *P* values < 0.05 will be considered to be statistically significant. After the follow-up of half of the cases, the interim analysis will be conducted to evaluate the validity of the main results.

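### Lung ultrasound outcome: the formal definition is the T0-to-T3 change, the Background names the 24-h score, and neither is reliably precise without adjustment for T0 (minor, secondary outcome)

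*Protocol article*

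**What the plan says.** All of this is in the protocol article.

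- **Primary and secondary outcomes** gives the formal definition: "Changes between preoperative and postoperative LUSs in patients". The scale is also set there: "The LUS score (0–36) is then calculated by adding up the 12 individual quadrant scores", with higher scores worse.
- **Background**, in its closing list of other outcomes, names "lung ultrasound scores 24 h after surgery", a level at a single time.
- **Related parameter setting during operation** fixes the measurements: "Lung ultrasound scores (LUSs) will be performed at T0 and T3". Both forms can therefore be computed from the same data.
- **Table 3** has one row for the T0 score and one for the T3 score, and no row for the change.
- **Statistics** says that quantitative variables will be "analyzed by using the analysis of variance (ANOVA) or Mann-Whitney" U test. It names no baseline covariate and does not say which lung ultrasound form is tested. The threshold is that P "values < 0.05 will be considered to be statistically significant".

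**The concern.** The T3 score and the change are different variables, and a between-group test of each can give a different p-value on the same patients. Lung ultrasound is the plan's measure of postoperative atelectasis and its only imaging evidence on the lung aim. With about 44 evaluable patients, a chance T0 difference between arms can move one or both results. As the article is worded, an analyst could find text to support either form after seeing the data. Neither form is a safe choice on precision: which one is better depends on a T0-T3 correlation that the documents do not give, and both ignore information that is already collected.

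**Working it through.** **The plan's own figure.** The only sample size is for cerebral oxygen saturation: "The difference in brain oxygen saturation before and after surgery was 3.6 ± 4.1", α = 0.05, β = 0.2. A two-sample t calculation (two-sided, standardized difference 3.6/4.1 = 0.878) gives 21.37, so 22 per arm and 44 in total. This matches the plan, and the sample size is not in dispute here. Recruitment is 54, or 27 per arm. No SD, effect size or correlation is given for lung ultrasound.

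**Assumptions.** k = SD(T0)/SD(T3) from 0.5 to 1; r = T0-T3 correlation from 0.2 to 0.7; roughly normal scores; two-sided 0.05. Neither k nor r is in the documents.

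**Same target.** Randomization makes the expected T0 difference between arms zero, so the expected group difference in T3 equals that in T3 − T0.

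**Variance of the group difference**, in units of the variance for T3 alone:

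- T3 alone: 1
- change: 1 + k² − 2rk
- T3 adjusted for T0 (large sample): 1 − r²

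Ratios to the adjusted analysis at the extremes of the range:

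- Change, k = 1, r = 0.2: (1 + 1 − 0.4)/(1 − 0.04) = 1.60/0.96 = 1.67
- Change, k = 0.5, r = 0.5: (1 + 0.25 − 0.5)/(1 − 0.25) = 0.75/0.75 = 1.00
- T3 alone, r = 0.2: 1/0.96 = 1.04
- T3 alone, r = 0.7: 1/0.51 = 1.96

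The adjusted variance never exceeds either. With k = 1 the change beats T3 alone only when r is above 0.5.

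**Disagreement on significance.** Simulation used 20,000 trials per setting, 27 per arm, and a true effect of 0.777 SD, which gives 80% power on T3 alone.

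| k | r | Power, T3 alone | Power, change | Forms disagree on p < 0.05 |
|---|---|---|---|---|
| 0.5 | 0.2 | 80% | 78% | 11–12% |
| 0.5 | 0.3 | 80% | 82% | 11–12% |
| 0.5 | 0.5 | 80% | 90% | 12–13% |
| 1 | 0.2 | 80% | 60% | 29% |
| 1 | 0.3 | 80% | 66% | 27% |
| 1 | 0.5 | 80% | 80% | 23% |
| 1 | 0.7 | 80% | 95% | 20% |

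Results with 22 per arm, where checked (k = 1), are almost the same.

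**No true effect.** The two test statistics correlate at (1 − rk)/√(1 + k² − 2rk). Under a bivariate normal, the chance that at least one form reaches p < 0.05 is 7.2% to 9.4% rather than 5%.

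**Response to a chance T0 imbalance d.** T3 alone shifts by (r/k)d and the change by (r/k − 1)d. The signs are opposite only when r < k. At k = r = 0.5 the change does not shift at all; at k = 0.5, r = 0.7 both shift the same way.

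**Why adjustment reconciles the wordings.** If T3 = a + τ·group + β·T0 + error, then T3 − T0 = a + τ·group + (β − 1)·T0 + error. The estimate of τ and its standard error are identical. This identity is linear and does not carry over to ranks: in 4,000 simulated trials per setting, rank analysis of covariance on T3 and on the change disagreed on significance in about 5% (k = 0.5, r = 0.5) to 9% (k = 1, r = 0.3).

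**The case against.** The contradiction is thin. The outcomes section is the formal definition and states one outcome. The Background sentence is a list of variables without metrics and can be read as naming the postoperative measurement. Table 3 is a descriptive shell that also holds urine volume and tumor size, and Table 2 presents the primary outcome, also defined as changes, by time point only. Baseline adjustment of a secondary outcome is often left to an analysis plan, which may exist. The patients are ASA I–II without chronic lung disease, so T0 may vary little; at k = 0.5 the change is within 10% of the adjusted variance (1.00 to 1.09).

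Most of this stands, and it limits the point. A reader might infer that the plan sets up two rival outcomes of equal standing, so that the sponsor may report whichever is favourable. The documents do not support that: the outcomes section normally governs over a Background list, and Table 3 does not make T3 alone a planned test. A reader might also infer that the two forms always respond in opposite ways to a T0 imbalance; that is true only when r < k.

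What remains is that the two wordings differ, nothing in the article reconciles them, and the stated tests are unadjusted for either form. The Background also reports alveolar collapse before operation in 15–20% of patients, so negligible T0 variation cannot be taken for granted.

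**Conclusion.** The point holds as a minor one on a secondary outcome. The formal definition is the change; the Background wording should be brought into line with it. Because both forms share the same true group difference, conflicting verdicts would come from sampling variation and precision, not from different effects. Relative to T3 adjusted for T0, the change has 1.00 to 1.67 times and T3 alone 1.04 to 1.96 times the variance. With 27 per arm and the effect used above, the two would disagree on p < 0.05 in about 11% to 29% of trials. These sizes rest wholly on the assumed k and r and on approximate normality. If T0 scores cluster near zero, k is small and disagreement falls toward or below the low end.

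**What to change.** 1. Reword the Background item so that it names the same lung ultrasound outcome as the outcomes section.
2. State one analysis, before unblinding: the T3 score compared between arms by linear analysis of covariance with the T0 score as covariate. The treatment estimate is then the same whether the outcome is written as T3 or as the change, so the two wordings agree.
3. If a rank-based sensitivity analysis is wanted, fix in advance that it ranks T3 with T0 as covariate, because ranking the change is a different analysis.

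The cost is one or two sentences. Both scores are already scheduled, SPSS fits the model, and no visit, measurement or treatment changes.

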**Discussion:**

This study aims to determine whether protective lung ventilation during dura opening can improve rSO_2_ and the state of pulmonary ventilation in patients undergoing intracranial tumor surgery, and to investigate whether this strategy affects the degree of brain tissue swelling and the reoperation rate after operation. If our results are positive, this study will show that protective lung ventilation during dura opening can be used effectively and safely in neurosurgical patients undergoing craniotomy for tumor resection.

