## Discussion

This study is a single-center, randomized controlled trial exploring whether protective lung ventilation (PLV) during intraoperative dura opening can improve regional cerebral oxygen saturation (rSO_2_) in neurosurgical patients.

The incidence of postoperative pulmonary complications (PPCs) is high due to the long mechanical ventilation in neurosurgery. Qaseem et al. [24] reported that the risk of PPCs increased when the operation time is more than 4 h. The incidence of PPCs was 28.4% (20.2–37.9%) in patients with neurosurgery lasting for longer than 300 min [25]. PEEP can lower the incidence of postoperative respiratory complications, prevent atelectasis, and reduce the risk of ventilators associated with lung injury.

In this study, individual PEEP (< 10cmH_2_O) will be used to avoid the effect of high PEEP on intracranial pressure (ICP). It is a crucial issue that PEEP can be safely used in craniotomy. Therefore, pulmonary protective ventilation will be performed during dura opening, and cerebral relaxation will be assessed before dura incision. If the ICP is elevated enough to affect the operation for using PEEP, we will abandon the case and change the ventilation parameters. The case will be reported to the principal investigator.

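### Brain relaxation is defined as a score taken before the arms differ in treatment, and no score is scheduled while PEEP is applied

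*Protocol article*

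**What the plan says.** Under Primary and secondary outcomes, brain relaxation is a 4-point score (1 completely relaxed, 4 bulging), "which will be scored by the neurosurgeons after opening the cranium and before opening the dura". The Discussion agrees on that timing: "pulmonary protective ventilation will be performed during dura opening, and cerebral relaxation will be assessed before dura incision".

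Other places give two time points. The section Related parameter setting during operation says: "The degree of brain relaxation at T1 and T2 will be evaluated by the surgeon using the brain relaxation scale". The Abstract (Methods) and Table 3 also list both T1 and T2. T1 is before the dura is opened and T2 is after it is closed.

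The same section limits the intervention to one window. The protective arm receives the lower tidal volume "combined with individualized PEEP during intraoperative dura mater opening", "but in other periods of general anesthesia, VT will be set at 8 ml/kg of predicted body weight", which is the control arm's tidal volume. It adds: "Titration can only begin once the dura is opened".

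The Abstract (Discussion) states the aim that this outcome serves: "to investigate whether this strategy affects the degree of brain tissue swelling and the reoperation rate after operation".

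**The concern.** A score can reflect the intervention only if it is taken during or after exposure. The definition under Primary and secondary outcomes places the score before exposure begins. A comparison of the arms on that score tests whether randomization balanced the groups, not whether PEEP affects the brain.

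Brain relaxation is the only listed outcome that directly grades swelling, and the Background gives the reason to look: PEEP may reduce cerebral venous return and the surgeon's working space. The Discussion treats safe use of PEEP in craniotomy as crucial. At stake is whether the trial can answer its own question about swelling while PEEP is in use.

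The document also gives two timings for one outcome, T1 alone or T1 and T2, and does not say which score, or which change, is the outcome.

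**Working it through.** No figure in the protocol underlies this point, so the check sets the scoring times against the intervention window.

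| Stage | Control arm | Protective arm | Relaxation score |
|---|---|---|---|
| T1, cranium open, dura intact | 8 ml/kg, PEEP 0 | 8 ml/kg, titration not yet allowed | Yes (all sources) |
| Dura open, titration | 8 ml/kg, PEEP 0 | 6 ml/kg, PEEP stepped from 0 to 10 cmH2O | None |
| Dura open, individual PEEP | 8 ml/kg, PEEP 0 | 6 ml/kg with selected PEEP | None |
| T2, dura closed | 8 ml/kg, PEEP 0 | 8 ml/kg, no PEEP named for this period | Yes (Abstract, intervention section, Table 3); absent from the outcome definition and the Discussion |

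**Step 1: T1.** Up to T1 both arms follow the same ventilation plan. With random allocation, expected difference at T1 = E(score, P arm) − E(score, C arm) = 0, whatever PEEP does later. A test at the 5% level can then be significant only by chance, or through a difference in care before the dura is opened. T1 has no sensitivity to swelling caused by PEEP.

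**Step 2: the intervention window.** Titration has 11 levels (0 to 10 cmH2O) of 1 minute each: 11 × 1 = 11 minutes, followed by the individual PEEP until the dura is closed. Relaxation scores scheduled in this window: 0. The Abstract (Objective) names two points inside the open-dura period, Ta after opening and Tb before closing, but only for cerebral oxygen saturation. The text schedules no relaxation score at either. The schedule figure is not shown in the copy reviewed.

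**Step 3: T2.** T2 follows exposure, so it can carry an effect of the intervention, but only one that persists after the window ends. That PEEP has stopped by T2 is an inference: the text names PEEP only for the open-dura period and does not state when it is withdrawn.

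**Step 4: who has a T2 score.** Termination criteria remove patients with markedly raised intracranial pressure or brain swelling during surgery. Withdrawal from the trial lists severe swelling as a reason to consider withdrawal. The Discussion says that a case is abandoned if PEEP raises intracranial pressure enough to affect the operation. These patients may have no T2 score. With 54 patients allocated 1:1, each arm has 54 / 2 = 27, so each removal takes 1 / 27 = 3.7% of an arm, and it takes those most likely to score badly. If PEEP does cause swelling, a T2 comparison of the remaining patients leans toward no harm.

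**The case against.** The strongest reply is that T2 is scheduled in three places. With T1 it gives a baseline and a post-exposure score by randomized arm. That stands. A reader might infer from the outcome definition that the trial cannot detect any effect of PEEP on swelling, but the documents do not support this: the lack of sensitivity holds for T1 only.

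Nor can T2 be dismissed because the brain is covered. The dura is also intact at T1, where the protocol applies the same scale.

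A reader might also infer that nothing about swelling is captured during PEEP. Gross swelling would lead to termination or withdrawal, and all adverse events are recorded. These records matter, but they are not a graded, blinded, scheduled comparison between arms.

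Two further inferences go too far. The protocol does not call brain relaxation its key safety outcome: it is fifth of six secondary outcomes, and the primary outcome is cerebral oxygen saturation. The protocol also does not say that a null result at T1 will be taken as evidence of safety. Table 3 sets T1 beside T2 as one would a baseline, and the Discussion sentence can be read as a check before exposure.

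None of this supplies a score during PEEP or resolves the conflict between the two timings.

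**Conclusion.** The point holds in this form. As defined, the secondary outcome is a pre-intervention baseline with an expected between-arm difference of zero. The T2 score conflicts with that definition. It can show only swelling that outlasts the window, and it may be missing for the patients who matter most. No score is scheduled while PEEP is applied, so the stated aim on swelling is met only in part.

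This rests on three assumptions: care before the dura is opened is the same in both arms, although the anesthesiologist knows the allocation; PEEP ends with the open-dura period; and removed patients are not scored at T2, which the text leaves open. If they are scored, the bias at T2 falls away, but the gap during PEEP remains.

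The primary outcome is not affected. The missing observation cannot be recovered once the dura is closed, and the trial is recruiting, so a correction is worth more the earlier it is made.

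**What to change.** 1. Reconcile the Abstract, the intervention section, Primary and secondary outcomes, Table 3 and the Discussion so that all give the same scoring times.
2. Label T1 as the baseline score.
3. Add one score by the same blinded surgeon with the dura open, just before closing (Tb). Ta is a poor choice: it is defined only as after dura opening and could precede the 11-minute titration. Confirm that the scale is suitable with the dura open, since the protocol defines it for use before opening and the source of the scale is not at hand.
4. Name the Tb score alone as the secondary outcome, compared between arms with an ordinal model adjusted for T1. Keep T2 as supportive. Add this model to the Statistics section.
5. Keep patients removed for swelling in the comparison under their randomized arm, for example by assigning the worst category, and report such removals by arm.

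The cost is a protocol amendment and one short extra score from a surgeon who is already present and blinded, on a scale already in use. Patients already operated on will have no Tb score, so that comparison will cover only part of the sample. The change concerns measurement and analysis only; no ventilation setting or clinical rule is altered.
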